### MRI protocol

Patients will finish brain MRI at baseline and 6 weeks after whole training. MRI will be performed using an optimized protocol, using the 3.0-T MRI scanner (Siemens Healthcare, Prisma, Germany). Functional MRI data collected will be analyzed using the Statistical Parametric Mapping (SPM) (UCL Queen Square Institute of Neurology, London, UK). Brain activation and connectivity changes between the baseline and ending of training will be compared among four groups.

### Outcome assessment

All participants from two hospitals will be assessed by neuropsychologists who have received consistent training, and brain MRI examinations will be performed using the same MRI scanner.

### Data management

This experiment will keep the data strictly confidential and stored in Alibaba Cloud through eCRF, and each person in our team has a personal account for data entry and revises. The background of eCRF has a correction function to prevent some errors. This trial collects behavioral data and nuclear magnetic data, not biological data. The datasets analyzed and the informed consent form during the current study are available from the corresponding author on reasonable request.

### Data monitoring

The project management group is composed of [name] and [name]. The group is mainly responsible for managing the overall work of the two centers and reviewing every 6 weeks. The trial auditing group is composed of two staff members of the audit department and is responsible for regularly reviewing the progress, authenticity, and safety every 6 weeks. [name] is independently responsible for all data monitoring of the study. The intervention may produce mild adverse events, such as headache and irritability, which can be improved by giving the patient rest or interval stimulation. If the patients show unbearable, they can opt out of the trial. We should report this situation to the supervisory department for record. The trial auditing group and the independent Data Monitoring and Ethics Committee have to review conduct throughout the trial period.

### Sample size

The hypothesis is 77.2% response rate in the cognitive training group and 41.4% in the control group on our preliminary studies [32]. The difference between the two groups was improved about 35.8%, as the basis for calculation. With a statistical power of 80% and a significance level of 5%, the minimum sample size of 28 subjects is required in each group. With our previous research experience, we allow for a maximum dropout rate of 20%. The study adopts the block randomization to divide into groups with 8 patients in each block. The actual minimum sample size of each group was 34 cases. Combining each center clinical states, Beijing center inclusion number has been set to 120 patients to participate into this research and Shenyang center has 80 patients.

### Statistical analysis

The analysis will be conducted on the basis of the intent-to-treat (ITT) principle. Some descriptive analysis of the data gathered during each assessment will be carried out precisely until the final assessment. Special time points for analysis are the baseline, end of iTBS or sham iTBS sessions, and 3 and 6 months after the final treatment. Median and range describe continuous variables, and frequencies and percentages describe qualitative variables.

We will accept a significance level of 5% (*P* < 0.05) corrected for multiple comparisons when needed. To assess our primary endpoint criterion, i.e., cognitive performance changes on the task, outcomes at four time points will be compared using repeated measurement analysis of variance of variance with time (baseline, ending, and 3 and 6 months after the final treatment) and group (study group (iTBS+WMT), WMS control group (iTBS+SRT), iTBS control group (sham iTBS+WMT), and placebo control (sham iTBS+SRT)) as factors. Further comparison between the two groups can show the simple iTBS effect, the simple WMT effect, and the facilitation effect of iTBS on WMT. Sensitivity analyses will explore the impact of imputation of data losses including loss to follow-up and dropout.

In the case that the data do not meet the normal distribution assumption, the non-parametric Mann-Whitney test will be used to compare performance improvements between four groups. SPM will be used to analyze imaging data to detect any changes in brain function and structure caused by cognitive training.

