**Discussion:**

The aim of our study is to explore the facilitation effects of iTBS added on WMT in improving cognitive function of schizophrenia. That means, patients with schizophrenia will benefit more in cognitive function improvement from the combination training mode of “preheating (iTBS stimulation changes the neural activity of working memory-related brain regions) and ironning (working memory training).” And the long-term effects of this combined training model will be assessed at a 6-month follow-up period. In case of a significant improvement of working memory with a prolonged effect, the iTBS combined with WMT protocol could be considered as a first-line clinical protocol in schizophrenia treatment. More broadly, the potential for increased universality and efficiency of rTMS with the iTBS model to enhance the neural plasticity of the brain should have a more positive effect on cognitive function in schizophrenia.

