### Primary outcome measures

The primary outcome measures are cognitive function measured by the MATRICS Consensus Cognitive Battery (MCCB).

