### Neuropsychological assessment

Cognitive function: MATRICS Consensus Cognitive Battery (MCCB) and Wechsler Adult Intelligence Test Brief Version (WAIS-R) as special measures for evaluating cognitive function in schizophrenia.
1.1Evaluation indicators of primary training effect (working memory): spatial span, digital sequence, verbal memory (Hopkins Verbal Learning and Memory Test (HVLT)), visual memory (Brief Visuospatial Memory Test (BVMT)).1.2Evaluation index of migration effect:
1.2.1Psychomotor speed: symbol code; trial making A; category fluency1.2.2Reasoning and problem solving: maze test1.2.3Social cognition: emotion management, verbal emotion recognition test (VERT), face emotion recognition test (FERT)1.2.4Attention: continuous performance test (CPT)Clinical symptoms: the Chinese version of the Positive and Negative Symptoms Scale (PANSS), the Concise Negative Symptoms Scale (BNSS), and the Clinical Global Impression (CGI) were used to evaluate clinical symptoms through the semi-fixed inspection method. These were assessed by four clinical training senior physicians in each center.Social function: Personal and Social Performance Scale (PSP)Others: Quality of Life Scale (SQOLS), Temporary Pleasure Experience Scale (TEPS), Self-esteem Scale (SES), the visual analogue scale (VAS) of side effects

All the above scales were evaluated blindly by the raters, who were unaware of the treatment methods used by the patients. Except for the WAIS-R, which was evaluated only once at the baseline, the other scales were assessed at four time points (before and after the training and 3 and 6 months of follow-up).

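### The protocol gives three versions of the primary endpoint and fixes no primary score, visit or contrast, so 5% error control is not secured and the 80% power does not describe the planned analysis

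*Protocol article*

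**What the plan says.** All places are in the Protocol article.

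- Primary outcome measures: "The primary outcome measures are cognitive function measured by the MATRICS Consensus Cognitive Battery (MCCB"). No composite, domain, test or visit is named.
- Statistical analysis: "To assess our primary endpoint criterion, i.e., cognitive performance changes on the task", followed by "outcomes at four time points will be compared using repeated measurement analysis of variance" with time and group as factors. Pairwise comparisons then address the simple iTBS effect, the simple WMT effect and the facilitation of WMT by iTBS. None of the three is ranked first.
- Statistical analysis, on error control: "We will accept a significance level of 5% (*P* < 0.05) corrected for multiple comparisons when needed". No family, method or order is given.
- Sample size: "The hypothesis is 77.2% response rate in the cognitive training group and 41.4% in the control group", with 80% power and 5% significance, leading to 28 per group and 34 after dropout. Response is not defined, and the Statistical analysis section contains no responder analysis.
- Neuropsychological assessment: four indicators of the "primary training effect (working memory): spatial span, digital sequence, verbal memory" and visual memory, then eight indicators of a migration effect.
- Abstract, Discussion: the combination could be considered a first-line protocol "In case of a significant improvement of working memory with a prolonged effect".

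**The concern.** A battery, an unnamed task and a responder proportion are three different endpoints. A trial could succeed on one and fail on another, and the text does not say which one decides. Nor does it say which of the three post-baseline visits, or which of the three effects, carries the primary claim. The decision to correct for multiplicity is left open.

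Two things are at stake. First, if the deciding score, visit or contrast can be chosen once results are known, the nominal 5% no longer bounds the chance of a false positive claim. Second, the power statement compares two proportions, cognitive training against control. The planned analysis is a repeated-measures ANOVA on cognitive performance in four arms. The primary objective is facilitation, and the natural comparison for that is between two arms that both receive WMT.

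**Working it through.** **1. The plan's own sample size.** Inputs from Sample size: 77.2% and 41.4%, 80% power, 5% (two-sided assumed; the text does not say).

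- Arcsine formula: h = 2·asin(√0.772) − 2·asin(√0.414) = 0.748; n = 2(1.960 + 0.842)²/0.748² = 28.05, which matches the stated 28.
- Pooled two-proportion formula, mean proportion 0.593: n = [1.960·√(2·0.593·0.407) + 0.842·√(0.772·0.228 + 0.414·0.586)]²/0.358² = 28.4, so 29.
- Dropout: 28 × 1.2 = 33.6, so 34, as stated.

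The figure reproduces, but only for one comparison of two proportions, which the Statistical analysis section does not contain.

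**2. The endpoint in the three sections that should agree.**

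| Section | Endpoint | Score | Visit | Contrast |
|---|---|---|---|---|
| Primary outcome measures | MCCB cognitive function | not named | not named | not named |
| Statistical analysis | change on the task | not named | four time points, none primary | three effects, none primary |
| Sample size | binary response | not defined | not named | training vs control |

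**3. Number of tests available.** From Neuropsychological assessment: 4 working-memory indicators + 3 psychomotor speed + 1 reasoning + 3 social cognition + 1 attention = 12. There are three post-baseline visits and three contrasts.

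**4. Chance of at least one p<0.05 with no true effect and no correction, at one visit and one contrast.** For k independent tests this is 1 − 0.95^k: 1 − 0.95⁴ = 18.5% and 1 − 0.95¹² = 46.0%. For correlated tests I simulated equicorrelated normal statistics, two-sided at 1.96. The correlations are assumed; the protocol gives none.

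| Inter-test correlation | 4 tests | 12 tests |
|---|---|---|
| 0 | 18.5% | 46% |
| 0.3 | 17% | 40% |
| 0.5 | 16% | 32% |
| 0.7 | 13% | 23% |

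**5. One score only.** If a result at any of three visits could count (assumed inter-visit correlation 0.6), the simulation gives 11.8%. If any of three contrasts could count (assumed correlation 0.5), it gives 12.5%. Both are about 12%.

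**6. The other end of the range.** One named score with one group-by-time test, or a correction that covers the whole family, gives 5%. The text allows both this and the rates in steps 4 and 5.

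**7. The first-line statement in the abstract.** It needs a working-memory gain that is also prolonged. I read this, as an assumption, as a favourable significant result on the same one of the four indicators at end of treatment and at 6 months (inter-test 0.5, inter-visit 0.6, no correction). The chance under no effect is about 2% for one contrast and about 6% if any of three contrasts counts (inter-contrast 0.5).

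**The case against.** The strongest reply is that the protocol does promise correction, and that its method, family and order are normally left to a statistical analysis plan, which may exist but is not shown. A repeated-measures ANOVA can also cover all visits in one group-by-time test. All of this stands, and it rules out several stronger readings that a reader might infer:

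- **That the 5% level is in fact broken.** The rates in steps 4 and 5 assume no correction, while the text says there will be correction where needed. The text is compatible with 5% and with much more.
- **That 12 tests are co-primary.** The word primary in Neuropsychological assessment sets trained ability against transferred ability, matching the direct and migration effects in Study design. It does not define the primary endpoint.
- **That the false positive risk is 66% or 91%.** Counting 4 or 12 tests over three visits and three contrasts (36 or 108 tests; correlations 0.5 between tests, 0.6 between visits, 0.5 between contrasts) does give those figures. But that replaces the planned ANOVA with separate visit tests and ignores the promised correction.
- **That the first-line statement would be triggered by chance far more often than 5%.** It concerns working memory only and requires persistence. Step 7 gives about 2% to 6%, and the abstract says only that the protocol could be considered.

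The reply does not remove the contradiction. An analysis plan can choose a correction method. It cannot reconcile a battery, an unnamed task and a response rate without changing what the protocol declares primary. The ANOVA covers the visits only once a score is named and the group-by-time term is made the primary test. The text does neither, and goes on to unranked pairwise comparisons.

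**Conclusion.** The point holds as a failure to fix the primary endpoint. Primary outcome measures, Sample size and Statistical analysis give three versions, with no primary visit or contrast and with correction left open. Control at 5% is therefore not secured, which is a weaker statement than saying it fails. The 80% power applies to a two-group comparison of an undefined response, not to the planned analysis.

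The possible size, if tests were run uncorrected, is about 13–19% over four indicators, 23–46% over 12, and about 12% for one score with a free choice among three visits or three contrasts. These figures rest on assumed correlations (0 to 0.7 between tests, 0.6 between visits, 0.5 between contrasts). The contradiction between the three sections rests on no assumption.

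**What to change.** Amend now, while recruitment is ongoing and before any unblinded data are seen.

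1. Name one primary score, either the MCCB composite or one defined working-memory score, with no later swap.
2. Name one visit: end of treatment, 6 weeks.
3. Name one contrast. For the facilitation objective this is iTBS+WMT versus sham iTBS+WMT, or the iTBS-by-WMT interaction if that is what the sponsor means by facilitation. The two are different questions and need different sample sizes, so the choice must be explicit.
4. Test it once at two-sided 5%, and use the same definition in Primary outcome measures and Statistical analysis.
5. Test the other key score and the 3- and 6-month visits in a fixed order. Label the remaining MCCB tests secondary, with Holm correction, and tie the abstract's conclusion to this sequence.
6. In Sample size, restate the power at the planned 50 per arm (200/4) for that endpoint and contrast. Alternatively, define response on that score and add the responder analysis to Statistical analysis.

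Cost: no new data, since the MCCB tests are already scheduled at all four assessments. Single subtests lose confirmatory status. The power must be recalculated, and for a continuous score that needs a mean difference and SD that the protocol does not give. Keeping all 12 tests primary is not a free alternative. With Bonferroni at 0.05/12 = 0.0042, and taking the protocol's own response rates as a guide, power at 40 completers per arm (50 less 20%) would be about 66%, against 92% for a single test at 5%.

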### Randomization

Participants will be randomly allocated to four groups: study group (iTBS+WMT), WMS control group (iTBS+SRT), iTBS control group (sham iTBS+WMT), and placebo control (sham iTBS+SRT) in a ratio of 1:1:1:1, with stratification. After patients have given their consent form, randomization will be performed by an independent and professional statistician who is blinded to the patient interventions using block randomization in R Programming (Mathsoft company, USA). Each center has its own enrollment time as a compatibility factor, and 8 patients in the vicinity of the enrollment time are used as a block. There are 15 blocks (total 120 patients) in Beijing Huilongguan Hospital and 10 blocks (total 80 patients) in Shenyang Anning Hospital. Then, the sealed randomization codes and intervention number are sent out to each hospital. Blinding will have to be broken only if a patient needs emergency handling. Once in this way, the participant will be managed as off-trial.

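### The primary repeated-measures ANOVA has no stated way to keep patients with a missing visit, uses baseline inefficiently and omits centre; a baseline- and centre-adjusted mixed model would serve better

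*Protocol article*

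**What the plan says.** The Statistical analysis section of the protocol article names the primary method and its structure: "outcomes at four time points will be compared using repeated measurement analysis of variance of variance with time". The factors are given in full, "with time (baseline, ending, and 3 and 6 months after the final treatment) and group", where group has the four randomised arms. Baseline is therefore one of four levels of the outcome. No covariate and no centre term is named.

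The same section declares: "The analysis will be conducted on the basis of the intent-to-treat (ITT) principle". Its only mention of imputation is: "Sensitivity analyses will explore the impact of imputation of data losses including loss to follow-up and dropout". It does not say how the primary analysis treats a patient with a missing visit.

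The Randomization section allocates "in a ratio of 1:1:1:1, with stratification" and sets the blocks by hospital: "There are 15 blocks (total 120 patients) in Beijing Huilongguan Hospital and 10 blocks (total 80 patients) in Shenyang Anning Hospital". The Sample size section expects losses: "we allow for a maximum dropout rate of 20" per cent.

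**The concern.** There are three separate weaknesses, of unequal weight.

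- **Missing visits.** Classical repeated-measures ANOVA needs a value at every level of time. A patient seen at baseline and end of treatment who misses month 6 contributes nothing unless the gap is filled. With imputation mentioned only under sensitivity analyses, the primary analysis as worded has no stated means of keeping that patient, although the section commits to intent-to-treat. The losses need not be random: the Dropping criteria section lists relapse or worsening that requires a change of antipsychotic. An analysis of completers could then be biased as well as less precise.
- **Baseline.** As a level of the outcome, baseline is adjusted for only in the way a change score adjusts. That is less efficient than a covariate. If the group main effect were the term read, it would include a visit at which no treatment effect can exist.
- **Centre.** Randomisation is blocked within hospital, and the model does not reflect this.

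Precision matters here. The Background cites training effects of only 0.38 overall and 0.29 for working memory, and the primary objective is an enhancement on top of training.

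**Working it through.** **1. The plan's own figure.** The Sample size section assumes "77.2% response rate in the cognitive training group and 41.4% in the control group", with 80% power and 5% significance (two-sided assumed). With mean proportion 0.593:

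n = [1.96·√(2·0.593·0.407) + 0.8416·√(0.772·0.228 + 0.414·0.586)]² / 0.358² = (1.96·0.6948 + 0.8416·0.6470)² / 0.1282 = 28.4, rounded up to 29.

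The arcsine formula gives 28.05. The stated 28 per group reproduces to within one patient. The stated 34 is 28 × 1.2 = 33.6 rounded up; 28/0.8 would give 35. This calculation concerns response proportions. It supplies no standard deviation, visit correlation or MCCB effect, so the present point does not depend on it, and steps 3 and 5 rest on assumptions.

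**2. Complete cases.** Inputs: 200 patients, four equal arms (50 each), dropout at its 20% maximum. 200 × (1 − 0.20) = 160, or 40 per arm. This counts dropouts only; patients who miss one visit and return would lower it further. As an illustration, assume the loss is spread evenly over the three post-baseline visits. Then 50 × (1 − 0.0667) = 46.7 per arm are seen at end of treatment but 40 are used, so the standard error at that visit is wider by √(46.7/40) = 1.08.

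**3. Baseline as outcome or covariate.** With common variance σ² and correlation r between visits (assumed):

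- change score: variance 2σ²(1 − r)
- baseline covariate: variance σ²(1 − r²)
- ratio: (1 + r)/2

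This gives 0.75, 0.80, 0.85 and 0.90 for r = 0.5, 0.6, 0.7 and 0.8.

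**4. Group main effect.** For a constant post-treatment effect δ, the average over four visits is (0 + δ + δ + δ)/4 = 0.75δ.

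**5. Size in power terms.** Simulated power (%) of a pairwise contrast at end of treatment: 4,000 trials per setting, 50 per arm, 20% random dropout by 6 months, no centre effect; d is the standardised effect. All of d, r and the dropout pattern are assumed.

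| d | r | Complete cases, change | Complete cases, baseline covariate | Available data, baseline covariate | The same plus centre |
|---|---|---|---|---|---|
| 0.35 | 0.5 | 35.0 | 43.4 | 49.5 | 49.2 |
| 0.35 | 0.7 | 51.8 | 57.1 | 64.1 | 63.9 |
| 0.5 | 0.5 | 60.8 | 71.9 | 78.6 | 78.4 |
| 0.5 | 0.7 | 81.0 | 86.6 | 91.4 | 91.4 |

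From the first power column to the last, the gain is 10 to 18 points. About 5 to 11 come from the baseline covariate and about 5 to 7 from keeping available data. The available-data analysis here is a regression at one visit, not the full mixed model, and random dropout cannot show any bias.

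**6. Centre.** A constant hospital difference adds the same amount to a patient's baseline and later scores, so it cancels in within-patient change and does not enter the time-by-group interaction. When centre was given 10% of the variance, adding it to the baseline-adjusted model raised power by 0.4 to 1.4 points. With no true effect (r = 0.6, 10% centre share), rejection was 4.6% for unadjusted change and 4.9% with baseline and centre.

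**The case against.** The strongest reply is that the article never says incomplete patients are excluded. It declares intent-to-treat, and its sentence on imputation could even mean that the primary analysis imputes and the sensitivity analyses test the effect of doing so. Details of missing-data handling are commonly left to a fuller document. This stands as far as it goes: a reader might infer that completer selection is a stated rule, and it is not. It is how the named method behaves if nothing is imputed. If the primary analysis does impute, the 160-patient figure and the missing-data share of the power gain do not apply. What remains is that the article positively names a method that does not deliver its own intent-to-treat commitment without a further step, and assigns no such step to the primary analysis.

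Second, the endpoint is described as change in performance, which points to the time-by-group interaction. Under randomisation that test is valid, so the baseline issue is one of precision. This also stands. The dilution in step 4 matters only if the group main effect is read, and the section does not say which term is primary.

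Third, a reader might infer that leaving out centre makes the test invalid or materially widens its standard error, or that different MCCB raters at each hospital make centre essential. The documents do not support this. Stable centre differences cancel in change, and the simulation showed neither inflated type I error nor a material loss of power. The Neuropsychological assessment section places four physicians in each centre only for the clinical symptom scales, while the Outcome assessment section describes consistent training for neuropsychologists at both hospitals.

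Finally, 20% is a maximum, and 40 per arm still exceeds the stated minimum of 28. That is true, but the 28 was derived for a difference in response proportions, not for the MCCB analysis.

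**Conclusion.** The point holds as a recommended improvement, not as a finding that the primary test is invalid. In order of weight:

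- The named method and the intent-to-treat statement are not reconciled for patients with a missing visit. Without imputation, complete cases could be 160 of 200 at maximum dropout.
- Using baseline as an outcome level costs precision. The available reduction in single-visit contrast variance is 15 to 25% for r of 0.7 to 0.5, or 10% if r is 0.8. The correlation is assumed.
- Omitting centre is a mismatch with the blocked randomisation, with little expected effect on precision.

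The 10 to 18 points of power are illustrative and set the full alternative against a complete-case change analysis.

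A mixed model should not be read as curing everything. It relies on missing at random, and with baseline as a covariate it still leaves out patients who have no post-baseline value.

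**What to change.** Replace the primary analysis with a likelihood-based mixed model for repeated measures on the three post-baseline visits, using all available post-baseline data. Include as fixed effects:

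- baseline score and baseline-by-visit;
- centre;
- visit;
- group, or equivalently iTBS, WMT and iTBS-by-WMT, with the treatment-by-visit interactions.

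Use an unstructured covariance across visits. State that the model assumes missing at random and omits patients with no post-baseline value. Keep imputation for sensitivity analysis, with at least one scenario in which missing outcomes are worse than missing at random implies. Which visit carries the primary contrast is a separate choice of estimand that this point does not settle.

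The cost is analysis wording and code: baseline scores, centre and all visits are already collected. Recruitment was ongoing when the article was written. If the change counts as a protocol amendment, the Trial status section requires notice to the sponsor and centres and ethics review, so it should be made and dated before unblinding.
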